### Trial population and recruitment

The investigators will collaborate with local representatives of KPAs and people within the kidney service to recruit the participants who are currently receiving haemodialysis therapy at the Hull University Teaching Hospitals NHS Trust kidney service. Healthcare professionals at the kidney unit will discuss study participation with the patients before obtaining formal informed consent.

The investigators will give potential participants a letter and the trial participant information sheet. Consent for participation in the trial will be collected via a formal Informed Consent Form authored by the investigators; the consent form will check candidates suitability against both inclusion and exclusion criteria (fit recruitment profile/ confirmation that situations have not changed since recruitment), and outline the specifics of the trial, what activity is included in the intervention sessions (methodology outline) and how both feedback and personal data will be collected and processed. All inclusion and exclusion criteria are given in Table 1. For Phase two, the focus group/semi-structured interview sessions will be conducted with people who meet the same inclusion and exclusion criteria as the main trial participants (Table 1), ensuring consistency in the target population.

**Table 1 Tab1:** Inclusion and exclusion criteria of the proposed trial.

Inclusion criteria	Exclusion criteria
18 years or older	Less than 18 years of age
regular haemodialysis therapy for at least three months	Haemodialysis for less than three months
	Planned kidney transplant within the intervention period
	Active malignancy
	Inability to complete study assessments from the clinical perspective
	Inability to complete the interventions from the clinical perspective
	Inability to use tablet and the CGT app Inability to consent to study

As this is a pilot study, the sample size is determined by the number of eligible patients in the participating haemodialysis unit. While formal age-matching between the intervention and control groups is not feasible due to the small sample size, we will strive for balance in baseline characteristics through randomisation. The primary aim of this pilot study is to assess feasibility and gather preliminary data to inform a future, larger randomised controlled trial.

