### Randomisation

Participants will be assigned to either the intervention or control group based on their pre-existing haemodialysis schedule. The dialysis unit operates two main haemodialysis therapy groups: group 1 (Monday, Wednesday, Friday) and group 2 (Tuesday, Thursday, Saturday). Each main group is further divided into three sub-sessions based on the time of day: morning, afternoon, and evening. This results in a total of six possible haemodialysis therapy routes:

Route 1: Monday, Wednesday, Friday; Morning.Route 2: Monday, Wednesday, Friday; Afternoon.Route 3: Monday, Wednesday, Friday; Evening.Route 4: Tuesday, Thursday, Saturday; Morning.Route 5: Tuesday, Thursday, Saturday; Afternoon.Route 6: Tuesday, Thursday, Saturday; Evening.

In Phase 3 of this pseudo-randomised controlled study with a parallel design, participants in each of the six routes will be allocated to either the intervention or control arm. To minimise potential bias and contamination between groups, all participants in a given route (e.g., Monday, Wednesday, Friday; Morning/Afternoon/Evening) will be assigned to the same study arm. This approach ensures that intervention and control group participants will not have overlapping haemodialysis schedules, reducing the likelihood of communication and influencing between groups.

The allocation of each route to either the intervention or control arm will be determined by the research team. This pseudo-randomisation method, while not truly random at the individual level, offers a pragmatic approach to group allocation given the scheduling constraints of the haemodialysis unit and the need to minimize potential bias between study arms.

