### Statistical analysis

Given the pilot nature of this study, our sample size is not based on formal power calculations. Instead, it is pragmatically determined by the number of eligible patients in our dialysis unit. The results will be used to estimate effect sizes and inform sample size calculations for a future, full-scale randomised controlled trial.

In Phase three, data will be analysed to test the effect of CGT intervention on the scores of baseline and follow-up assessments. All data analyses will be conducted in IBM SPSS Statistics for Windows, version 27.0 (or higher) software. Data will be directly entered into Microsoft Office Excel spreadsheets (version 2202) by investigators and study staff using all standard data management procedures. Descriptive statistics will be calculated according to the normality assumption, with means and standard deviations reported for normally distributed data, and medians and interquartile ranges reported for non-normally distributed data. Within-group comparisons between baseline and follow-up assessments for primary and secondary measurements will be analysed using repeated-measures analysis of variance (ANOVA). In contrast, independent ANOVA will be used for between-group comparisons. For additional explorative analyses, correlation and regression models can be used to analyse the effects of other factors (e.g. age, gender) on the cognitive decline between the baseline and follow-up assessments.

In addition to the primary and secondary outcome analyses, a sub-group analysis will be performed to explore the potential effects of the CGT intervention based on participants’ baseline memory function and executive function. Participants will be stratified into subgroups based on their performance on the cognitive test scores, and the intervention effects will be compared between these subgroups. This exploratory analysis may help to identify which patients are most likely to benefit from the CGT intervention and guide future research in this area.

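### The between-arm comparison is an unadjusted ANOVA although arms follow whole dialysis routes and age is unmatched; age and gender are left to an optional exploratory model that does not say whether arm is included

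*Protocol article*

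**What the plan says.** All references are to the protocol article.

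- **Randomisation.** "Participants will be assigned to either the intervention or control group based on their pre-existing haemodialysis schedule". There are six routes (two day groups by three times of day), and everyone in a route "will be assigned to the same study arm". "The allocation of each route to either the intervention or control arm will be determined by the research team"; no chance mechanism is described. The section concedes the point itself: "This pseudo-randomisation method, while not truly random at the individual level".
- **Trial population and recruitment.** "formal age-matching between the intervention and control groups is not feasible due to the small sample size". The section then relies on randomisation for balance in baseline characteristics.
- **Introduction.** The effect of kidney disease on cognition is described as additional to normal age-related impairment, so the article itself links age to cognition.
- **Statistical analysis.** Within-group change is tested by repeated-measures ANOVA, and "independent ANOVA will be used for between-group comparisons". No covariate is named for either. Age and gender appear once, as examples in additional exploratory work: "correlation and regression models can be used to analyse the effects of other factors (e.g. age, gender) on the cognitive decline". The text neither includes nor excludes arm from those models. The results are to supply effect sizes for a full-scale trial.
- **Outcomes.** The primary outcome is change in cognitive scores within the intervention group. The secondary outcomes compare the arms, and the paragraph after Table 2 also compares cognitive scores between arms at four months.

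**The concern.** When patients are randomised individually, an unadjusted arm comparison is unbiased and covariates mainly add precision. Here the arms are made of existing schedules, placed by investigators, so that protection is missing. Age is the characteristic the article singles out as unmatched, and the safeguard it offers, randomisation, does not operate at patient level under its own allocation section.

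The article names the method for the arm comparison and gives age and gender a different, optional role. This is therefore a choice it makes, not a detail held over for an analysis plan. At stake are the between-arm differences in cognition and quality of life, and the planning values taken from them. An age gap between routes could be read as an effect of the apps.

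There is a smaller second matter. If the exploratory regression were run without arm, part of any arm effect could appear as an age effect. The text leaves this open.

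**Working it through.** **The plan's own figure.** The only sample-size arithmetic is 30 recruited to the intervention arm so that 25 complete, allowing up to 20% dropout. 25 × 1.20 = 30; 25 / 0.80 = 31.25, so 32. The stated 30 is within two patients, and this point does not depend on it. No SD, alpha or effect size is given. I use 25 v 25 completers, which assumes no loss among the 25 controls.

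**1. How large could an age gap be?** The documents do not say. Assumptions: age SD 15 years (variance 225), six routes of 55/6 = 9.17 patients, three routes per arm, and intraclass correlation (ICC) of age within route from 0 to 0.20.

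Var(route mean) = 225 × [ICC + (1 − ICC)/9.17]; SD of the arm difference = √(2/3 × Var).

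| ICC | SD of arm difference (years) | P(gap > 5 years) | P(gap > 7.5 years) | P(gap > 15 years) |
|---|---|---|---|---|
| 0 | 4.04 | 0.22 | 0.06 | <0.001 |
| 0.05 | 4.80 | 0.30 | 0.12 | 0.002 |
| 0.10 | 5.45 | 0.36 | 0.17 | 0.006 |
| 0.20 | 6.56 | 0.45 | 0.25 | 0.02 |

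The ICC = 0 row shows that much of the spread is ordinary small-sample chance. The probabilities also treat the choice of routes as if it were random, which the article does not state.

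**2. What would a gap do to the arm comparison of change?** Expected bias = (age gap in SD) × (age–change correlation r). Simulation with 25 v 25 independent patients, change SD 1, no true arm effect, intervention arm younger, 1,500 runs per row:

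| Gap (SD) | r | Unadjusted bias (SD) | Error rate at nominal 5%, unadjusted | Same, age in model |
|---|---|---|---|---|
| 0 | 0.1 / 0.3 / 0.5 | about 0 | 5.7 / 4.3 / 5.5% | 5.5 / 5.1 / 5.1% |
| 0.5 | 0.1 / 0.3 / 0.5 | 0.05 / 0.15 / 0.24 | 6.3 / 8.5 / 13.1% | 5.9 / 5.3 / 5.0% |
| 1.0 | 0.1 / 0.3 / 0.5 | 0.09 / 0.30 / 0.49 | 5.8 / 17.3 / 39.0% | 4.1 / 4.8 / 6.1% |

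With age in the model the bias is about 0 throughout. The simulation error on a 5% rate is √(0.05 × 0.95/1500) = 0.6 percentage points, so at r = 0.1 the inflation is slight. At the assumed SD, a gap of 0.5 SD is 7.5 years and 1.0 SD is 15 years. By the first table, 15 years would be rare if routes were placed by chance.

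**3. Raw four-month scores.** Assume 0.05 to 0.10 MoCA point per year and a gap of 5 to 10 years: 0.05 × 5 = 0.25 and 0.10 × 10 = 1.0 point. With an assumed SD of 3, the standard error is 3 × √(2/25) = 0.85. Adjusting for a baseline score of assumed reliability 0.75 leaves about a quarter, 0.06 to 0.25 point, which is at most 0.25/0.85 = 0.29 of a standard error. In a change score, a stable age effect on level largely cancels; bias then needs age to predict four-month change.

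**4. The exploratory model, if arm were left out.** With a true arm effect of 0.5 SD and no age effect, the expected false age slope is −0.5 × (gap × 0.25)/(1 + gap² × 0.25): −0.06 at a gap of 0.5 SD and −0.10 at 1.0 SD (simulated −0.06 and −0.11). With arm in the model it is 0.

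**The case against.** The strongest reply is that this is a pilot. The article says its goal is to collect initial data and assess procedures rather than to test a hypothesis, and its primary outcome is change within the intervention group, which an age gap between arms cannot confound. Nothing shows that age differs by route. Exploratory analyses of schedule against outcome are planned, and a full model specification is often left to a document not shown here.

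Much of this stands. The point reaches only the between-arm comparisons, and the bias is a risk, not a demonstrated fact. What does not stand is that pilot status makes the arm comparison harmless: the Statistical analysis section sets out to test the effect of the intervention and to carry effect sizes forward.

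A reader might infer more than the documents support:

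- **That the exploratory regression pools the arms with no arm term.** The text is silent. The other factors it mentions can be read as factors besides the intervention. Leakage of an arm effect into the age result follows only if arm is omitted.
- **That patients chose their shifts.** The article says the schedules were pre-existing, not who chose them.
- **That small numbers are the wrong reason for not matching.** Small numbers plausibly do limit matching, as the ICC = 0 row suggests. The conflict in that section is its reliance on randomisation, not its remark about sample size.
- **That a shift of up to one MoCA point is to be expected.** That range holds only for raw four-month scores under assumed slopes and gaps.

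**Conclusion.** The point holds in limited form. A non-random arm comparison is planned without covariates, while the characteristic conceded to be unmatched is left to an optional model whose terms are not stated. If routes differ in age and age relates to the outcome, the between-arm differences and the effect sizes taken from them are biased.

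The size is unknown. Over the assumed range it runs from nothing, with no age gap, to about 0.5 SD at a full SD of age gap and a correlation of 0.5, a corner that is unlikely if routes fall by chance. More moderate assumptions (gap 0.5 SD, r = 0.3) give 0.15 SD and an error rate of 8.5%. Age SD, ICC, age slopes, score SD and reliability are all assumptions. The simulation ignores clustering by route. The within-group primary outcome is not affected by this point.

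**What to change.** 1. **Statistical analysis, between-arm comparison.** Replace the independent ANOVA by a model with arm, the baseline score, age (continuous) and gender, for each cognitive and quality-of-life score.
2. **Statistical analysis, exploratory models.** State that arm is included in any regression of change on age or gender.
3. **Trial population and recruitment.** Remove the reliance on randomisation for balance, since allocation is by schedule. Say that adjustment removes only measured age and gender differences, and not other route-level differences or clustering by six routes. The text should not suggest that adjustment makes up for the allocation.

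The cost is wording and two degrees of freedom for age and gender (48 to 46 residual with 50 completers), plus one for the baseline score. Age and gender are already named in the article, and baseline scores are already collected.

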## Abstract

Disruptions in cognitive function have been reported in individuals undergoing haemodialysis and those with chronic kidney disease. This pilot study protocol primarily assesses the feasibility and acceptability of using mobile cognitive gaming apps for patient-led cognitive training during haemodialysis sessions. The protocol consists of three phases: (1) reviewing and evaluating available cognitive gaming apps, (2) conducting focus groups/interviews with people with kidney disease to determine app preferences, and (3) undertaking a quasi-experimental randomised controlled trial to compare cognitive outcomes between a patient-led app intervention group and a standard care control group over four months. Primary outcomes will include changes in cognitive test scores [Montreal Cognitive Assessment (MoCA), Modified Mini-Mental State Exam (3MSE), Rapid Objective Working Memory Assessment (ROWMA)], while secondary outcomes will encompass quality of life measures [Patient-Reported Outcomes Measurement (PROM) Kidney Disease Quality of Life Short Form (KDQoL-SF™) v 1.3, Patient-Reported Outcomes Measurement Information System (PROMIS) Global Health Instrument, European Quality of Life Five Dimension (EQ-5D)]. If demonstrated to be effective, this novel method of utilising gamified cognitive training applications could potentially mitigate cognitive decline and improve the well-being of people receiving haemodialysis without necessitating significant clinical resources. The findings from this research will guide the development of a larger definitive randomised trial in the future.

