### Trial treatment, data collection and analysis

#### Phase one: researcher review and evaluation of CGT apps in the marketplace

Collect and evaluate brain training apps from Google Play and the App Store. For the purpose of this study, brain training apps are operationally defined as mobile applications that provide non-invasive, readily accessible, and self-directed gamified cognitive tasks targeting various cognitive domains, including memory, attention, problem-solving, and processing speed^29^. These apps are designed to actively engage users with game-like exercises during dialysis sessions, encouraging them to independently practice their cognitive functions. The selection process will involve collecting and evaluating brain training apps available on Google Play and the App Store based on their adherence to this operational definition and their suitability for use in the haemodialysis setting at the unit.Shortlist apps based on their usefulness for cognitive training. While gaming apps may offer an accessible and engaging approach during haemodialysis sessions, it is important to note that their validity compared to standard cognitive assessments administered by trained professionals has not been established specifically in the haemodialysis population. Therefore, we will use validated cognitive assessment tools (MoCA, 3MSE) as our primary outcome measures, with the gaming apps serving primarily as an engagement tool during treatment sessions rather than a cognitive assessment instrument.All data collection and analysis in Phase one will be conducted by the investigators, without patient involvement.

These areas will guide the development of specific questions, which will be refined based on input from the research team and piloting with a small group of patients. This approach will ensure a comprehensive assessment of app usefulness while allowing flexibility to explore emerging themes during discussions. Focus groups/semi-structured interviews will be conducted by trained members of the research team, including study investigators and research assistants.

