Rapid Objective Working Memory Assessment (ROWMA)	Assesses working memory	Scores vary; higher scores indicate better working memory function	Baseline and 4 months	5–10 min	Computerised test
Kidney Disease Quality of Life Short Form (KDQoL-SF™)	Kidney disease-specific quality of life measure	0-100 for each subscale; higher scores indicate better quality of life	Baseline and 4 months	10–15 min	Includes generic and kidney disease-specific components
PROMIS Global Health Instrument	Brief measure of general health-related quality of life	T-score metric (mean = 50, SD = 10); higher scores indicate better health	Baseline and 4 months	5–10 min	Assesses physical, mental, and social health
European Quality of Life 5-D (EQ-5D)	Generic measure of health status	Index value 0–1; higher scores indicate better health status	Baseline and 4 months	5–10 min	Provides health utility scores for economic evaluations

*Score ranges and interpretations are based on general population normative data unless otherwise specified. Specific cutoff values and interpretations for the haemodialysis population may differ and are currently not well established. This highlights the exploratory nature of using these assessment tools in our specific.

Examining and comparing the cognitive and behavioural test scores of the intervention and control groups at the four-month assessments will provide insight to expand the scope and area of CGT intervention to other haemodialysis units. Feasibility outcomes will include patient recruitment and retention rates, adherence to the intervention (app usage frequency and duration), and the occurrence of any technical issues or adverse events. Acceptability will be assessed through semi-structured interviews with a subset of intervention group participants, exploring their experiences, satisfaction, and perceived benefits and challenges of using the CGT apps. If the feasibility and acceptability of CGT intervention are demonstrated, we will apply for further funding so that the CGT intervention can be delivered to more people receiving haemodialysis.

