No formal power calculation was conducted because this pilot study focuses on evaluating the feasibility and acceptability of using CGT apps in individuals undergoing haemodialysis. The primary goal of this pilot trial is to collect initial data and assess the study procedures rather than testing a specific hypothesis with a predetermined level of statistical power. The results from this pilot study will guide the design and sample size calculation for a future, larger scale definitive randomised controlled trial.

While our sample size limits a detailed analysis of the impact of different dialysis schedules, we will collect data on each participant’s schedule (Monday-Wednesday-Friday or Tuesday-Thursday-Saturday, and shift time). We will conduct exploratory analyses to examine potential associations between schedule and outcomes. This information will be valuable for designing a larger future trial where schedule effects could be more robustly analysed.

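### Feasibility is the stated purpose, but the outcomes labelled primary are cognitive tests (two in one section, three in others), and the pilot's imprecise effect size is to inform the next trial's sample size

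*Protocol article*

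**What the plan says.** **Purpose.** The Abstract says "This pilot study protocol primarily assesses the feasibility and acceptability of using mobile cognitive gaming apps". The recruitment section says "The primary aim of this pilot study is to assess feasibility and gather preliminary data to inform a future, larger randomised controlled trial". The Statistical analysis section says "The primary goal of this pilot trial is to collect initial data and assess the study procedures rather than testing a specific hypothesis", and the sentence goes on to qualify this by reference to a preset level of power. That section gives the feasibility focus as its reason for having no power calculation. Other sections mix the aims: the Research question asks about feasibility and potential impact together, Aims and objectives lists the effect on cognitive decline first, and Trial design names both feasibility and effectiveness.

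**Outcomes.** The Abstract says "Primary outcomes will include changes in cognitive test scores" and lists MoCA, 3MSE and ROWMA. The Outcomes section names the same three, as change from baseline in the intervention group. The Phase one text says "we will use validated cognitive assessment tools (MoCA, 3MSE) as our primary outcome measures". Recruitment, retention, adherence, technical issues, adverse events and acceptability interviews come at the end of Outcomes, labelled neither primary nor secondary. The next step is tied to them: "If the feasibility and acceptability of CGT intervention are demonstrated, we will apply for further funding".

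**Analysis and use.** In Phase three "data will be analysed to test the effect of CGT intervention on the scores of baseline and follow-up assessments", by within-group and between-group ANOVA. Also: "The results will be used to estimate effect sizes and inform sample size calculations for a future, full-scale randomised controlled trial".

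**The concern.** A pilot may go without a power calculation because efficacy is not its main question. This article relies on that exemption and still gives the primary label, and planned tests, to efficacy outcomes. A report that follows the labels would lead with cognitive results that the trial was never sized to establish, while the measures on which the funding decision depends would carry no rank.

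The two versions of the primary set leave ROWMA's status open, so its result could be promoted or demoted after the data are seen.

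The effect-size plan carries the problem into the next trial. A standardised difference from about 50 patients is imprecise. Here it is also open to bias, because whole dialysis routes are allocated by the research team and the assessors are unblinded. A definitive trial sized on a chance high estimate would be too small.

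**Working it through.** **Labels side by side**

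| Section | First-ranked item |
|---|---|
| Abstract, opening | Feasibility and acceptability |
| Abstract, outcomes | MoCA, 3MSE, ROWMA |
| Research question | Feasibility and potential impact |
| Aims and objectives | Effect on cognitive decline |
| Trial design | Feasibility and effectiveness |
| Trial population and recruitment | Feasibility and preliminary data |
| Phase one | MoCA, 3MSE |
| Outcomes | MoCA, 3MSE, ROWMA (within the intervention group) |
| Statistical analysis | Initial data and study procedures; tests of cognitive effect |

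No section makes a feasibility measure a primary outcome.

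**Sample-size inputs.** The Participant withdrawal section gives 55 patients: 30 intervention (up to 20% dropout, at least 25 completers) and 25 control. The stated 30 is 25 × 1.2. Dividing by the retained share gives 25/0.8 = 31.25, so 32, and 30 × 0.8 = 24. I therefore use 25 v 25 as the planned case and 24 v 20 if both arms lose 20% (25 × 0.8 = 20).

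**Precision of the pilot effect size.** For an unadjusted between-group standardised difference near zero, with patients treated as independent, SE = √(1/n₁ + 1/n₂).
- 25 v 25: √(2/25) = 0.283; 95% limits ±1.96 × 0.283 = ±0.55 SD.
- 24 v 20: √(1/24 + 1/20) = 0.303; limits ±0.59 SD.
- Six routes of about 50/6 = 8.3 completers, design effect 1 + 7.33 × ICC. At an assumed ICC of 0.01 it is 1.07 and the limits are ±0.57 SD; at 0.05 it is 1.37 and the limits are ±0.65 SD.

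**Consequence for the next trial.** Assume a true effect of 0.3 SD, two-sided 5%, 80% power and a two-sample t test. The document states none of these.
- Needed at 0.3 SD: 176 per arm.
- Estimate one SE high: 0.3 + 0.283 = 0.583, which gives 48 per arm.
- Power with 48 per arm at the true 0.3 SD: 31%.
- Estimate one SE low: 0.3 − 0.283 = 0.017, from which no trial can be sized.

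A simulation of 25 v 25 pilots at a true 0.3 SD, sizing the next trial on the observed estimate (normal approximation), gave a 10th to 90th percentile range of about 33 to 978 per arm. Of the pilots with a usable estimate (above 0.05 SD), 61% led to a trial with less than 79% power. In about 19% of all pilots the estimate was 0.05 SD or lower.

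**Power of the pilot's own between-group test** (t test, 25 v 25): 18% at 0.3 SD and 41% at 0.5 SD.

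**The case against.** The strongest reply is that the aim is mixed rather than misdescribed. The Research question, Aims and Trial design sections all include a cognitive effect, so a cognitive outcome is not foreign to the study. This stands: the fault is a split purpose with the labels on one side, not a pure feasibility study given the wrong outcomes.

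Some stronger readings are tempting but not supported:
- *No hypothesis is to be tested.* The sentence in Statistical analysis disclaims a test with preset power, and the Abstract and recruitment section do not disclaim testing at all. Exploratory ANOVA does not flatly contradict it. The tension lies in testing outcomes that are called primary.
- *Nothing is measured that could decide feasibility.* Outcomes names several such measures. Only their rank is missing. Numerical progression thresholds may sit in the full protocol, and their absence from an article is no fault.
- *The pilot point estimate will be the next trial's target difference.* The text says that the results will inform the sample size, which is looser. It does not rule that use out either, and effect sizes are what it names.
- *A poor cognitive result would stop the next trial.* Outcomes ties the next step to feasibility and acceptability.
- *Multiplicity.* Three tests at 5% could give up to 1 − 0.95³ = 14.3% chance of a false positive, but the article states no alpha and the tests are probably correlated, so this is a ceiling and the point does not rest on it.

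The two-versus-three conflict may be loose wording, since the Phase one sentence contrasts validated tests with gaming apps. But it says primary outcome measures outright, and Outcomes counts ROWMA among its validated instruments.

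Finally, the SE above is for a between-group contrast, whereas Outcomes defines the primary change within the intervention group. The between-group figure is still the one that matters for a future controlled trial.

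**Conclusion.** The point holds as a conflict of labels and uses within the article. Feasibility is given as the main purpose and as the reason for having no power calculation; cognitive change is labelled primary and tested; the feasibility measures are unranked; and the primary cognitive set has two versions. These rest on the text alone.

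The effect-size part rests on arithmetic: limits of about ±0.55 SD at 25 v 25, wider with dropout in both arms or with route clustering. The 48 v 176 per arm and the 31% power depend on the assumed 0.3 SD and on conventional alpha and power; they illustrate the risk and do not predict the result. The lack of a power calculation is acceptable in a pilot and is not criticised. The change should be made, because it alters what the pilot can conclude.

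**What to change.** 1. In the Abstract and Outcomes, make recruitment, retention and adherence the primary outcomes, each reported with a 95% CI.
2. Use one cognitive list in the Abstract, the Phase one text and Outcomes. Label it secondary and report it as between-group estimates with CIs rather than as tests of effect. This also gives the cognitive outcomes the control comparison that the present definition lacks.
3. In Statistical analysis, say that the pilot supplies the SD, baseline correlation, retention and adherence for planning, and that the future target difference will be a minimum important difference, with the pilot CI used only as a plausibility check.

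I do not propose retention cut-offs. The 20% in the article is a recruitment allowance, not a success criterion, and 24 of 30 retained has a 95% Wilson interval of 63% to 90%. Nor should the next trial rely on a route ICC from this pilot: six routes in two arms leave 6 − 2 = 4 between-route degrees of freedom.

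The cost is wording in four sections and no new data. The sponsor gives up a headline efficacy claim from the pilot.
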